# ctDNA guided adjuvant chemotherapy versus standard of care adjuvant chemotherapy after curative surgery in patients with high risk stage II or stage III colorectal cancer: a multi-centre, prospective, randomised control trial (TRACC Part C)

**DOI:** 10.1186/s12885-023-10699-4

**Published:** 2023-03-20

**Keywords:** Colorectal cancer, ctDNA, Adjuvant chemotherapy, Randomised, Disease free survival

## Abstract

**Background:**

Circulating tumour DNA (ctDNA) to detect minimal residual disease (MRD) is emerging as a biomarker to predict recurrence in patients with curatively treated early stage colorectal cancer (CRC). ctDNA risk stratifies patients to guide adjuvant treatment decisions. We are conducting the UK’s first multi-centre, prospective, randomised study to determine whether a de-escalation strategy using ctDNA to guide adjuvant chemotherapy (ACT) decisions is non-inferior to standard of care (SOC) chemotherapy, as measured by 3-year disease free survival (DFS) in patients with resected CRC with no evidence of MRD (ctDNA negative post-operatively). In doing so we may be able to spare patients unnecessary chemotherapy and associated toxicity and achieve significant cost savings for the National Health Service (NHS).

**Methods:**

We are recruiting patients with fully resected high risk stage II and stage III CRC who are being considered for ACT into the study which uses results from a plasma-only ctDNA assay to guide treatment decisions. Eligible patients are randomised 1:1 to receive ctDNA-guided chemotherapy versus SOC chemotherapy. The primary endpoint is the difference in DFS at 3 years between the trial arms. Secondary endpoints include the proportion of patients in the ctDNA-guided arm who are ctDNA negative post-operatively and receive de-escalated ACT compared to the standard arm, the difference in overall survival (OS), neurotoxicity and quality of life between the arms, and the cost-effectiveness of ctDNA-guided therapy compared to SOC treatment. We hypothesise that using a ctDNA-guided approach to ACT decisions is non-inferior to SOC. Target accrual is 1621 patients over 4 years, which will provide a power of 80% with an alpha of 0.1 to demonstrate non-inferiority with a margin of 1.25 in survival of the ctDNA-guided approach compared to SOC. We anticipate approximately 50 UK centres will participate. The study opened with the Guardant Reveal plasma-only ctDNA assay in August 2022.

**Discussion:**

The trial will determine whether ctDNA guided ACT is non-inferior to SOC ACT in patients with fully resected high risk stage II and stage III resected CRC, with the potential to significantly reduce unnecessary ACT and the toxicity associated with it.

**Trial registration:**

NCT04050345.

## Introduction

Colorectal cancer (CRC) is the fourth most prevalent cancer in the UK accounting for more than 11% of all new cancer diagnoses [1], with 42,900 patients being diagnosed every year [2]. More than 60% of these patients have early stage disease (stage I, II or III) which is potentially curable [3]. The mainstay of treatment for patients with early colon cancer is surgery, plus adjuvant chemotherapy (ACT) in those whose tumours demonstrate high risk histopathological features for recurrence [4]. Early rectal tumours may be managed with surgery alone, or with neo-adjuvant radiotherapy with or without concurrent chemotherapy, followed by surgery in those with high risk features. This may be followed by ACT if patients have not received neo-adjuvant chemotherapy in the context of total neo-adjuvant treatment (TNT) [5].

The 5 year disease free survival (DFS) for patients with stage II and III colon cancer treated with surgery without ACT is 81.4% and 49.0% respectively [6], with the risk of recurrence being highest in the first 2 years following surgery [7]. ACT aims to help reduce the risk of future recurrence by targeting potential micrometastatic disease. Current standard management of patients with resected high risk stage II and stage III CRC is 3 to 6 months of fluoropyrimidine (FP)-based ACT. ACT treatment decisions are made based on the stage and histopathological features of the resected tumour together with consideration of the patient’s clinical situation including performance status (PS). Accordingly, patients may receive 3 to 6 months of FP chemotherapy in combination with oxaliplatin; oral capecitabine plus oxaliplatin (CAPOX) every 3 weeks for 4 cycles or infusional 5-fluorauracil plus oxaliplatin (FOLFOX) every 2 weeks for 12 cycles. Alternatively, those with a poorer PS and/or lower risk histopathological features may receive 6 months of FP monotherapy, either capecitabine or 5-fluorauracil.

In stage III disease, treatment with a FP reduces the risk of cancer recurrence by 41% [8], with a further 6.9% absolute improvement in 3 year DFS from the addition of oxaliplatin [9]. Oxaliplatin-based treatment comes at a cost, however. In one study of 346 patients, 89% of patients experienced at least one symptom of acute neuropathy (e.g., sensitivity to the cold) with the first cycle of oxaliplatin. After 18 months, only 19% patients reported more than 30% reduction in symptoms according to the Chemotherapy-Induced Peripheral Neuropathy (EORTC QLQ-CIPN20) sensory scale [10]. In stage II disease, ACT with FP improves survival by 3.6% [11] with oxaliplatin offering a 5% absolute improvement in 3 year DFS [9].

The UK SCOT study established that reducing ACT duration with CAPOX from 6 to 3 months did not compromise 3 year DFS and reduced the toxicity burden of treatment [12]. These results were later pooled with other global randomised trials in the International Duration of Adjuvant Therapy (IDEA) collaboration which reported a 0.4% difference in 5 year OS, concluding 3 months of CAPOX was non-inferior to 6 months. As a result, 89.5% clinicians changed practice to offer 3 months of chemotherapy for some patients, continuing to preference 6 months of treatment in high risk stage III patients [13]. This is now widely considered the standard of care (SOC) ACT regimen for patients with fully resected CRC. Despite this evidence, it is likely that we are still over treating many patients with ACT, who may be cured with surgery alone.

Currently considerations regarding the need for ACT include histopathological features of the resected tumour and other patient factors such as age, comorbidities, PS and patient preference, leading to shared decision making. ctDNA has emerged as a biomarker for minimal residual disease (MRD) and can predict early relapse, offering a tailored approach to individual decision making [14]. Stage II patients who are ctDNA negative post-operatively have been shown to have a 3 year recurrence free survival (RFS) of 90% compared to 0% in those who are ctDNA positive [15]. Similarly in stage III disease 3 year RFS is 76% and 47% respectively [16]. Recent data from an observational registry, suggests that ACT in patients who are ctDNA negative makes little difference to DFS [17] and is potentially exposing patients to unnecessary toxicity which could be safely avoided. By reducing or omitting needless treatment in post-operative ctDNA negative patients, they may be spared the short and long-term side effects of treatment, multiple hospital visits, as well as the potential psychological impact of treatment. Should this study be positive and adopted into standard practice, there could be huge cost-saving implications for the National Health Service (NHS).

We hypothesise that ACT decisions guided by the post-operative ctDNA result will enable biomarker driven selection of patients who would and would not benefit from ACT, and thereby reduce the proportion of patients receiving ACT without compromising DFS. The primary objective is to demonstrate that a de-escalation strategy of ctDNA guided adjuvant chemotherapy is non-inferior to SOC chemotherapy as measured by 3 year DFS in patients with high risk stage II or stage III resected CRC with no evidence of MRD (i.e., those who are ctDNA negative post-operatively).

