#### Arm B: ctDNA guided ACT

For patients randomised to ctDNA guided ACT, the post-operative (Month 0) blood sample will be processed in real time and the result will be published on the Guardant Health online portal. The recommended SOC chemotherapy regimen will continue to be used in patients who are ctDNA positive post-operatively, whilst ACT will be de-escalated in those who are ctDNA negative. Where 3 months of CAPOX has been recommended, treatment will be de-escalated to 3 months of capecitabine alone, and where 6 months of capecitabine monotherapy has been recommended, treatment will be de-escalated to no chemotherapy. Patients who are ctDNA negative post-operatively and have their chemotherapy de-escalated (Fig. 2) will undergo a further blood test for ctDNA post-ACT or 3 months after the post-operative sample in those who are not receiving ACT. Patients who remain ctDNA negative at the post-ACT (Month 3) timepoint will continue to follow up. If ctDNA becomes positive, chemotherapy will be escalated to 3 months of CAPOX in all patients. A CT scan will also be performed to rule out radiological macroscopic disease.

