## Discussion

We describe the protocol of the multi-centre, prospective, randomised trial designed to compare the 3 year DFS in patients with high risk stage II and stage III fully resected colon and rectal cancers treated with ctDNA guided ACT versus SOC chemotherapy, sponsored by the Royal Marsden Hospital NHS Foundation Trust, London. The study builds on the results from TRACC Part B; the observational, prospective, translational research study involving serial blood sampling for ctDNA pre- and post-operatively, which demonstrated an improved 12 and 24 month RFS in patients who were ctDNA negative post-operatively.

TRACC Part C is the only ctDNA-guided study of ACT in CRC running in the UK and addresses a research question with significant health economic importance. The DYNAMIC II study is the only reported study in this space to date globally, which provided evidence to support the de-escalation of ACT in patients with resected stage II colon cancer [21]. We anticipate that the results of this study, together with the DYNAMIC II study and similar ongoing studies across the world will generate the evidence to support the clinical utility of ctDNA in the MRD de-escalation setting, generating support for a change to standard practice. In doing so, it may spare patients unnecessary chemotherapy and its associated toxicities and saeg the health service significant costs, redirecting resources elsewhere. The use of chemotherapy in this setting may halve.

TRACC Part C is one of the only ctDNA-guided studies using a plasma-only tumour-naïve ctDNA assay for MRD detection in CRC globally. Utilising a blood-only assay with a turnaround time of 7-14 days, where analysis of tumour tissue is not required, lends itself to a more streamlined approach to recruitment within the study, as well as smooth potential future implication into standard clinical practice. The inbuilt patient reported outcomes (PROs), health economic analysis and process evaluation will provide a route to effective implementation in SOC clinical practice within the NHS and elsewhere in the future.

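### No listed endpoint measures the hypothesised fall in the proportion of patients receiving adjuvant chemotherapy

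*Protocol article*

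**What the plan says.** The Introduction states the hypothesis in terms of who receives ACT at all: guidance will "thereby reduce the proportion of patients receiving ACT without compromising DFS". Just before that, the rationale is put more broadly: "By reducing or omitting needless treatment in post-operative ctDNA negative patients".

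The section on the ctDNA-guided arm sets two de-escalation steps for ctDNA-negative patients:

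- "Where 3 months of CAPOX has been recommended, treatment will be de-escalated to 3 months of capecitabine alone"
- "where 6 months of capecitabine monotherapy has been recommended, treatment will be de-escalated to no chemotherapy"

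It then adds a return to treatment at the Month 3 sample: "If ctDNA becomes positive, chemotherapy will be escalated to 3 months of CAPOX in all patients".

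Two places define the endpoint on treatment use, and they differ:

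- The Secondary endpoints section takes the share of the guided arm that is given SOC ACT. A second item there, also confined to the guided arm, covers conversion to ctDNA positive with escalation.
- The Abstract (Methods) takes patients who are "ctDNA negative post-operatively and receive de-escalated ACT compared to the standard arm".

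The Discussion adds: "The use of chemotherapy in this setting may halve".

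**The concern.** The hypothesis concerns receipt of ACT, but neither version of the endpoint counts it. Under the Secondary endpoints wording, a patient switched from CAPOX to capecitabine is no longer on SOC ACT and so leaves the numerator, although that patient receives three months of chemotherapy. There is also no SOC-arm figure, so SOC patients who decline or never start ACT are not allowed for. Under the Abstract wording, less ACT and no ACT are pooled, and the arm named as comparator has no ctDNA-guided de-escalation because its ctDNA results are not returned in real time.

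Sparing patients chemotherapy is one of the trial's headline aims. If DFS non-inferiority is shown, the companion statement will be how many patients were spared. A figure for SOC ACT could then be taken as a figure for ACT avoided, and the two can be far apart.

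**Working it through.** **Inputs.** From the protocol: eligibility requires every patient to be due to receive ACT, so intended ACT in the SOC arm is 100%. The two regimens are 3 months of CAPOX or 6 months of capecitabine. The planned size is 810 per arm. Not in the protocol, and therefore assumed:

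- n = share of the guided arm that is ctDNA negative after surgery (range 0.7 to 0.9)
- p = share of those ctDNA-negative patients for whom CAPOX was recommended (range 0.3 to 0.9)
- full adherence, and no Month 3 escalation

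The protocol states no figure of its own for this endpoint, so there is none to reproduce.

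**Formulas for the guided arm at first allocation.**

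- Receiving SOC ACT: 1 − n. Fall from 100%: n.
- Receiving any ACT: (1 − n) + n·p = 1 − n(1 − p). Fall from 100%: n(1 − p).
- Overstatement if the first fall is read as the second: n − n(1 − p) = n·p.

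**Results at n = 0.8.**

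| p | SOC ACT | Any ACT | Fall in SOC ACT | Fall in any ACT | Overstatement |
|---|---|---|---|---|---|
| 0.3 | 20% | 44% | 80 points | 56 points | 24 points |
| 0.5 | 20% | 60% | 80 points | 40 points | 40 points |
| 0.7 | 20% | 76% | 80 points | 24 points | 56 points |
| 0.9 | 20% | 92% | 80 points | 8 points | 72 points |

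Over the whole assumed range, the fall in SOC ACT is 70 to 90 points and the fall in any ACT is 7 to 63 points. The SOC ACT figure does not depend on p, so it carries no information about how many patients had chemotherapy omitted. Month 3 escalation would lower the fall in any ACT further.

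**The halving remark, read as patients receiving any ACT.** This needs n(1 − p) ≥ 0.5, that is p ≤ 1 − 0.5/n: 28.6% at n = 0.7, 37.5% at n = 0.8, 44.4% at n = 0.9.

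**Could the trial estimate the right quantity?** Take 76% against an assumed 95% in the SOC arm, with 810 per arm. The 95% half-width is 1.96 × √(0.76 × 0.24/810 + 0.95 × 0.05/810) = 1.96 × 0.0168, or about 3.3 points. Precision is not an obstacle.

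**The case against.** The strongest reply is that the endpoint is labelled SOC ACT and measures SOC ACT. The article is open that the strategy is de-escalation, its rationale speaks of reducing as well as omitting treatment, and both steps are spelled out. The benefit of dropping oxaliplatin is already compared between arms through neurotoxicity, quality of life and cost-effectiveness. Tables of treatment received may also sit in the full protocol or SAP, which are not shown. Much of this stands, and it limits the point to a mismatch between a hypothesis and its endpoint. It does not remove the mismatch: the article does state the endpoint, states it in two ways, and neither matches the hypothesis sentence.

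The Abstract phrase can also be read as ACT that is lighter than the standard arm's, with no comparison of proportions intended. On that reading too, reduced and omitted ACT are pooled.

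Four stronger readings are tempting but not supported:

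- **That most de-escalation is CAPOX to capecitabine.** The Introduction presents 3-month CAPOX as widely accepted standard care and monotherapy as the alternative for poorer performance status or lower-risk features, which points towards a high p. But no split is given, and stopping six months of treatment altogether can equally be called the larger step.
- **That the hypothesis cannot be answered.** The per-protocol analysis needs treatment received in both arms, and escalation has its own endpoint, so receipt of any ACT by arm could be derived. It is simply not listed.
- **That the result will look better than it is.** This follows only if SOC ACT is read as ACT avoided.
- **That the halving remark is wrong.** It is hedged, and use of chemotherapy could mean agents or volume rather than patients treated.

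**Conclusion.** The point holds in a limited form: the article hypothesises a lower proportion receiving ACT, and no listed endpoint measures it. The two endpoint definitions disagree, and the one in the Secondary endpoints section removes every CAPOX-to-capecitabine switch from the count although the patient received ACT.

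The possible overstatement is n × p. Its size rests wholly on two assumed shares, on full adherence and on no escalation, so the figures illustrate the gap and do not predict it. This is a secondary-endpoint matter that should be corrected; the primary DFS inference is untouched.

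**What to change.** 1. Reconcile the Abstract and the Secondary endpoints section into one definition.
2. Make that endpoint the between-arm difference, with confidence interval, in the proportion of all randomised patients who receive any adjuvant chemotherapy, counting Month 3 escalation.
3. Report SOC ACT, de-escalated ACT and no ACT separately by arm, together with receipt of oxaliplatin.
4. Align the hypothesis sentence and the halving remark with the broader rationale of reducing or omitting treatment, so that omission is claimed only where chemotherapy was omitted.

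The cost is wording in the protocol and analysis plan. Treatment received is already needed for the per-protocol analysis. The one real downside is a headline reduction less favourable than the SOC ACT figure.

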## Methods

### Study design

TRACC Part C is a multi-centre, prospective, randomised study of patients with resected high risk stage II and stage III CRC who have undergone curative surgery with an R0 resection designed to demonstrate non-inferiority of ctDNA guided ACT versus SOC chemotherapy. Patients with rectal cancer who have undergone neo-adjuvant radiotherapy with or without concurrent chemotherapy (but not TNT) are also eligible. A list of participating sites is available at Tracking Mutations in Cell Free Tumour DNA to Predict Relapse in Early Colorectal Cancer—Full Text View—ClinicalTrials.gov. Eligible patients are randomly assigned to receive either ctDNA guided ACT (intervention; Arm A) or SOC chemotherapy (comparator; Arm B) (Fig. 1). Randomisation in a 1:1 ratio is performed centrally at the Institute of Cancer Research – Clinical Trials and Statistical Unit (ICR-CTSU), by random permuted blocks, with results communicated by telephone. The randomisation will be stratified by the following factors: high risk stage II versus stage III, and site of primary tumour (right colon versus left colon versus rectum).

**Fig. 1 Fig1:**
[figure not shown]
Study schema for TRACC Part C

### Study population

Patients are eligible if they are 18 years or over, have histologically proven high risk stage II or stage II CRC that has been fully resected with clear margins (> 1 mm), Eastern Cooperative Oncology Group (ECOG) PS 0–2 and able to give informed consent. Patients must have adequate organ function as determined by routine full blood count and biochemistry blood tests, and no evidence of metastatic disease on pre- or post-operative imaging, with the absence of major post-operative complications. Patients should be assessed by an oncology team and deemed suitable for treatment with ACT, having a post-operative blood sample for ctDNA collected 4–8 (+ 2) weeks after surgery in four 10.0 ml Streck cfDNA BCT® whole blood collection tubes and commencing ACT within 12 weeks. The inclusion and exclusion criteria are outlined in Table 1. Eligible patients will receive a patient information leaflet at least 24 h prior to consent and then be required to sign a written informed consent form. Consent will be taken by a clinician who is familiar with counselling patients and prescribing ACT for CRC. Successfully recruited patients who fulfil the eligibility criteria will be randomised to receive SOC ACT or ctDNA guided chemotherapy.

**Table 1 Tab1:** TRACC Part C eligibility criteria

Inclusion criteria	Exclusion criteria
1. Subject ≥ 18 years of age 2. Subjects with histologically proven high-risk stage II or stage III colon or rectal cancer treated with curative intent with surgery alone (any T, N1 or N2) with no evidence of metastatic disease. High-risk stage II is defined as having one or more of the following: T4 disease, tumour obstruction and/or perforation of the primary tumour during the pre-operative period, inadequate nodal harvest as indicated by < 12 nodes examined, poorly differentiated grade on histology, perineural invasion, peritoneal involvement or extramural venous/lymphatic invasion. Subjects must be due to receive adjuvant chemotherapy following surgery Subjects with histologically proven locally advanced rectal cancer treated with neoadjuvant chemoradiotherapy (any T, N1 or N2, M0) with no evidence of metastatic disease are eligible. Subjects must be due to receive adjuvant chemotherapy following surgery 3. Fully surgically resected tumour (R0) with clear resection margins (i.e., > 1 mm) 4. Adequate organ function - Absolute neutrophil function ≥ 1.0 × 10^9^/ L - Platelet Count ≥ 75 × 10^9^ / L - Haemoglobin ≥ 80 g/L (blood transfusion before randomisation is allowed) - Adequate renal function as calculated by Cockcroft and Gault equation (GFR ≥ 50 ml/min if single agent capecitabine or CAPOX being administered) - Aspartate aminotransferase/ Alanine aminotransferase levels ≤ 2.5 upper limit of normal 5. Absence of major post-operative complications or other clinical conditions that, in the opinion of the investigator, would not contraindicate adjuvant chemotherapy 6. Patients should be assessed by Oncology team for suitability and assessment for adjuvant chemotherapy, be able to have post-operative ctDNA sample collected and be randomised by week 4–8 (± 2 weeks) after surgery and commence adjuvant chemotherapy within 12 weeks after surgery 7. ECOG performance status 0- 2 8. Able to give informed consent	1. History of concurrent and previous malignancy within the last 5 years, with the exception of non- melanomatous skin cancer and carcinoma in situ 2. Any major post-operative complications or other clinical conditions that in the opinion of the investigator would contra-indicate adjuvant chemotherapy 3. Any subject not due to receive adjuvant chemotherapy will not be eligible for Part C of the study 4. Hypersensitivity or contraindication to the drug(s) associated with the planned choice of systemic chemotherapy (CAPOX or capecitabine) as stated in the Summary of Product Characteristics (SmPC) for each of the drugs 5. Subjects due to receive 5-flurouracil (5FU) based adjuvant chemotherapy (either single agent 5FU or in combination with oxaliplatin) will not be eligible for Part C of the study, these patients will continue to be followed in the observational Part B of the study

ECOG performance status, Eastern Cooperative Oncology Group performance status

